**7. Description of the treatment**

Patients will stop antiretroviral treatment for eight weeks and will return to it for eight to twelve additional weeks with the addition of interleukin-2 for six weeks.

This process will be repeated four times. Upon finishing the four cycles, treatment with IL-2 and ART will be suspended unless there has been evidence of viral replication to the point that viral load (VL) reaches a stable level. (Definition of point stabilization: equal VL in three sequential determinations separated by at least three weeks)

a) Doses, intervals, method and form of administration and duration

Interleukin-2 (IL-2), 125,000 units/m2/day, subcutaneously, for six weeks

b) Criteria for modifying the protocol during the trial:

 INTOLERANCE/TOXICITY

Interleukin-2: the tolerance of the medication will be evaluated at each visit with a view to its suspension in cases where the severity or intensity of adverse effects so prescribe.

 SAFETY MEASURES

Because of concerns over an eventual appearance of resistance and a loss of antiretroviral treatment efficacy, various measures have been designed to ensure that intermittent therapy will be immediately discontinued in case there is a failure to:

- Analyse the response to treatment in the weeks leading up to each interruption. VL will be measured at seven weeks after restarting treatment in each cycle. The study will be stopped if more than two favourable responding patients reach VL <50 copies/mL.

- The study will only be interrupted between weeks 64 to 80 in those patients who show lowered VL after the third interruption compared with the first interruption.

- ART will be started in patients with CD4+ lymphocyte count <350 cells/µL or with an HIV-1 plasma VL >55,000 copies/mL in two consecutive determinations (27). In asymptomatic patients with CD4+ lymphocyte count between 350-500 cells/µL and/or VL between the previous levels, the evaluation of resuming ART will be done on an individual basis.

- There will be a safety commission.

c) Concomitant medications:

Any concomitant medication will be reflected appropriately in the DCN (detailing the product, dose, administration method, day of administration, reason for the treatment, etc.).

1. Salvage medication:

ART will be started in patients with CD4+ lymphocyte count <350 cells/µL or with an HIV-1 plasma VL >55,000 copies/mL in two consecutive determinations (27).

The salvage medication will also be appropriately recorded in the DCN throughout the entire follow-up period of the trial.

1. Standards for handling trial drugs:

The pharmaceutical specialties used in the study do not require special conditions for conservation or handling, under normal conditions of humidity and temperature.

***

**8. Trial development and response evaluation**

a) Main evaluation variables (activity and effectiveness):

- To determine the proportion of patients with VL increases at least three times greater than the baseline (prior to ART) (corresponding approximately to an increase of 0.5 log).
- To determine the proportion of patients with specific cytotoxic response to HIV
- Compare the level of viremia stabilisation at stopping ART by comparing viremia at the end of the fourth cycle and at the end of the study with pre-HAART viremia.
- Determine the proportion of patients not requiring ART at the end of the study.

b) Secondary variables (safety and tolerance):

- Description of adverse events

c) Number and timing of visits and tests or examinations.

Medical visits will be carried out during the first week of the study, then every fortnight for four months and then every two months until the end of the study. During the periods of treatment interruption analyses will be carried out weekly. During the periods of treatment the analyses will be monthly.

An amygdala biopsy will be taken at the beginning and at the end of the study

See calendar (p. 18).

d) Duration of the study:

Two and a half years from the date of the first patient inclusion. The recruitment period should be two months and the duration of the study 24 months from the date of the last patient inclusion.

Calendar of the visits and tests or examinations.

| Determination | 0 | 8 | 16[[1]](#footnote-2) | 24 | 32 | 40 | 48 | 56 | 64 | 72 | 80 | 88 | 96 | 104 | 112 | 120 | 128 | 136 | >136 |
| --- | --- | --- | --- | --- | --- | --- | --- | --- | --- | --- | --- | --- | --- | --- | --- | --- | --- | --- | --- |
| VL (limit of detectability = 10) | a | a | a | a | a | a | a | a | a | a | a | a | a | a | a | a | a | a | Every 4 weeks |
| Complete blood count | a |  |  |  |  |  |  |  | a |  |  |  |  |  | a |  |  | a | Every 8 weeks |
| CD4 | a |  |  |  |  |  |  |  | a |  |  |  |  |  | a |  |  | a | Every 8 weeks |
| Histocompatibility[[2]](#footnote-3) | a |  |  |  |  |  |  |  |  |  |  |  |  |  |  |  |  |  |  |
| Cytotoxic function in response to HIV and CD4 helper function[[3]](#footnote-4) | a |  | a |  | a |  | a |  | a |  |  |  |  |  | a |  |  |  | Every 16 weeks |
| Integrated HIV DNA  In peripheral mononuclear cells (PMC) | a |  | a |  | a |  | a |  | a |  |  |  |  |  | a |  |  |  | Every 16 weeks |
| Plasma and PMC conservation | a |  | a |  | a |  | a |  | a |  |  |  |  |  | a |  |  | a | Every 8 weeks |
| Lymphoid tissue[[4]](#footnote-5) | a |  |  |  |  |  |  |  |  |  |  |  |  |  |  |  |  | a |  |
| Genotype resistance test | a | a |  | a |  | a |  | a |  | a |  | a |  | a |  | a |  | a |  |
| Blood in EDTA (ml) | 21 | 7 | 21 | 7 | 21 | 7 | 21 | 7 | 21 |  |  |  |  |  | 21 |  |  | 21 |  |
| Blood in ACD (ml) | 20 |  |  |  |  |  |  |  |  |  |  |  |  |  |  |  |  |  |  |

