Neumann et al. and Garcia et al. have reported triple treatment interruption therapies, with follow-up in patients until VL rebounded and reached stable levels, before returning to ART. In the 23 patients, control of VL was at least as quick during the second round of treatment as it was in the first round. All patients had a VL of <200 copies/mL at six weeks of the second course of treatment.

1. *Effects of IL-2 administration*

Numerous studies have looked at combining ART with three or more anti-retroviral drugs with cycles of IL-2 administered during five days in high (18 million UI/day) or intermediate (3-6 million UI/day) doses via i.v. or s.c. every eight weeks (14-23). This approach has been used in advanced patients (with CD4+ lymphocyte counts <200-500 cell/µL) with the aim of increasing the number of CD4+ lymphocytes, improving other immunological parameters and reducing the apoptosis of T lymphocytes. In addition, observations have shown that the concurrent administration of elevated doses of IL-2 and ART reduces the pool of latent CD4+ lymphocytes that contain the DNA of integrated HIV-1 (21). Nevertheless, when ART is stopped, there is a fast rebound of HIV-1 plasma VL (22). On the other hand, high or intermediate IL-2 doses have numerous side-effects, mainly when administered by i.v. (24). This toxicity is dose-dependent. There are no adverse effects when it is administered in low doses. In this sense, exceptional adverse effects were noted in a study of patients with neoplasia related to HIV-1 infection receiving low doses of IL-2 (0.5-1.2 million UI/day) for 3 months but, on the other hand, there were no observations of opportunistic infections or increases in HIV-1 plasma VL, embodying an immunological improvement of Th1 cell response (24).

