To evaluate the virological response and the specific cytotoxic response to HIV, the point of stabilisation of viremia after fourth cycle of interruption of anti-retroviral treatment (ART), and the proportion of patients who do not require ART at the end of study following the administration of subcutaneous, low doses of IL-2.

Specific aims:

- To determine the proportion of patients with VL increases at least three times greater than the baseline value (prior to ART) (corresponding approximately to an increase of 0.5 log).
- To determine the proportion of patients with specific cytotoxic response to HIV
- Compare the level of viremia stabilisation at the point of stopping ART by comparing viremia at the end of the fourth cycle and at the end of the study with pre-HAART viremia.
- Determine the proportion of patients not requiring ART at the end of the study.

***

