**12. Statistical analysis**

a) Statistical tests:

- Descriptive analysis:

The descriptive analysis will include variables referring to demographic data and clinical events related to the sample as well as adverse reactions in terms of absolute and relative frequency, means and standard deviations, medians and ranges.

*Indications for antiretroviral treatment*

Spanish recommendations for ART (27) prescribe that it should not be given to patients who are asymptomatic with CD4+ lymphocyte cell count <500 µg/L and a viral load <10,000 copies/mL. The proportion of patients presenting both criteria will be determined at two points: 1) when VL reaches the set-point following the last withdrawal from treatment; and 2) at the end of the study (week 120-136).

- Comparative Analysis

*1) Increase in plasma VL in the* ***eighth*** *week following withdrawal, and 2) proportion of patients with cytotoxic response to HIV.*

- Comparison will be made between cycles one, two, three and four.

An increase in VL is defined as being at least three times greater than the baseline (prior to ART) (corresponding approximately to an increase of 0.5 log).

- In patients with a VL <10 copies/mL (undetectable), an increase will be considered as being any value >20 copies/mL after two weeks since the interruption of treatment.

- A more sensitive analysis will compare the second, third and fourth cycles with the first cycle, for each patient, as paired data. McNemar’s test will be used to compare discordant results: i.e., N pairs with a higher value for the first cycle and a lower value for the fourth cycle, with the N pairs from the opposite situation. The same considerations will be applied to the evaluation of the cytotoxic capacity and function of CD4 *helper* lymphocytes, which will be recorded as positive vs. negative or good vs. weak versus according to the stimulation index.

*2) Analysis of VL increase time above 5,000 copies/mL.*

- The treatment will be stopped in weeks 64-80, if viremia in week 56 is less than in week eight.

- The increase time will be compared (measurement history) with that of other groups (see references 2 and 3)

3) *Multivariant analysis*

A ‘response’ is defined as the lack of a rebound or the absence of indications for ART on multiple occasions following the interruption of treatment.

The indicating response factors will be evaluated by means of multiple regression analysis, and will include:

- CD4 count before ART,

- VL before HAART,

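### The first viremia-stabilisation reading, at the end of the fourth cycle, falls on ART under Section 7 and before the final withdrawal, so it mainly shows drug suppression

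*Protocol*

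**What the plan says.** Section 4 (specific aims) and Section 8a (main evaluation variables) carry the same item in nearly the same words. Section 4 has "Compare the level of viremia stabilisation at the point of stopping ART by comparing viremia at the end of the fourth cycle" and Section 8a has "Compare the level of viremia stabilisation at stopping ART by comparing viremia at the end of the fourth cycle". In both, the sentence continues with a second reading at the end of the study, and both readings are compared with viremia before HAART.

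Section 7 fixes the order of events within a cycle: "Patients will stop antiretroviral treatment for eight weeks and will return to it for eight to twelve additional weeks". It then says "This process will be repeated four times", and "Upon finishing the four cycles, treatment with IL-2 and ART will be suspended", with an exception tied to viral replication. It defines stabilisation as three equal viral loads (VLs) in sequence, at least three weeks apart.

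The protocol describes the target differently elsewhere. The primary goal in Section 1.10 and the general aim in Section 4 place stabilisation after the fourth cycle of interruption. Section 12 judges the indication for ART first "when VL reaches the set-point following the last withdrawal from treatment", and again at weeks 120-136. Section 12 uses that set-point only for the proportion without an indication for ART, not for this viremia comparison.

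**The concern.** The variable is meant to show where viremia settles once ART is withdrawn. Under Section 7, its first reading comes at the close of a treatment block, before the final withdrawal has happened. Set against the level before any HAART, that value will be lower in patients whose ART works, whether or not IL-2 or the interruptions had any effect. The study has one arm, so no control group would expose this. An analyst following Sections 4 and 8 literally would report a fall in viremia under a label that promises control off treatment.

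**Working it through.** **1. When the fourth cycle ends.** Inputs from Section 7: 8 weeks off, then 8 to 12 weeks on, four cycles. End of cycle four = 4 × (weeks off + weeks on).

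- Shorter schedule: 4 × (8 + 8) = 64
- Longer schedule: 4 × (8 + 12) = 80

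This reproduces the final stop at weeks 64-80 given in Section 12.

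**2. ART status at that point.** The first footnote to the Section 8 calendar gives a different cycle: ten weeks, of which the first two are off treatment, so 10 − 2 = 8 weeks on. All three versions are shown.

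| Cycle (weeks off + on) | Fourth interruption | Fourth on-ART block | End of cycle four |
| --- | --- | --- | --- |
| 8 + 8 | weeks 48-56 | weeks 56-64 | 64, after 8 weeks on ART |
| 8 + 12 | weeks 60-68 | weeks 68-80 | 80, after 12 weeks on ART |
| 2 + 8 (footnote) | weeks 30-32 | weeks 32-40 | 40, after 8 weeks on ART |

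Each of these schedules ends the fourth cycle on ART.

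**3. Against the definition of stabilisation.** Three determinations at least three weeks apart span at least 2 × 3 = 6 weeks, so one end-of-cycle value cannot satisfy the definition. After the final withdrawal it cannot be met before week 64 + 6 = 70 or week 80 + 6 = 86. The first three calendar VLs after the stop are at weeks 72, 80 and 88 (stop at 64) or weeks 88, 96 and 104 (stop at 80).

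**4. What the VL is likely to be.** Section 6a requires VL below 50 copies/mL for at least eight months on HAART. For the interruption experience in 23 patients, Section 4 reports: "All patients had a VL of <200 copies/mL at six weeks of the second course of treatment". The block here lasts 8 to 12 weeks.

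The protocol gives no pre-HAART VL. As an illustration only, assume 10,000 to 100,000 copies/mL before HAART and 50 to 200 copies/mL on ART:

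- smallest fall: log10(10,000 / 200) = 1.7
- largest fall: log10(100,000 / 50) = 3.3

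**5. The second reading.** Weeks 120-136 (Section 12) set against the planned stop:

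- stop at 64: 120 − 64 = 56 to 136 − 64 = 72 weeks off ART
- stop at 80: 120 − 80 = 40 to 136 − 80 = 56 weeks off ART

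This applies to patients who were withdrawn and had not restarted.

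**The case against.** The strongest reply is that the protocol does not use cycle in one sense. Sections 1.10 and 4 speak of a cycle of interruption. Section 12 compares cycles one to four on VL in the eighth week after withdrawal, an off-ART value. Its stopping condition uses weeks 8 and 56, which on the 8 + 8 schedule are the ends of the first and fourth interruptions. Section 1 also counts four six-week cycles of IL-2. On these usages the first reading could mean the end of the fourth interruption, off ART.

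This stands as evidence that the time point is ambiguous and that an off-treatment level was probably intended. It does not remove the problem. Section 7 is the only place that lays out a full cycle for all four rounds, and there the cycle closes on ART. Sections 4 and 8 also tie the item to the stopping of ART, which fits the end of the on-ART block. Even the end of the fourth interruption is not the set-point in Section 12, because a further 8 to 12 weeks of ART follow before the last withdrawal.

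A reader might infer that the whole variable measures drug suppression. The documents do not support that, because the same sentence includes the end-of-study reading, which is off ART for patients not restarted. A reader might also infer that the trial's main result is invalid. That goes too far: Section 1.13 lists three main variables and this is not among them, although Section 8a lists it as main and Section 1.10 puts stabilisation in the primary goal. No success threshold is attached to the comparison.

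**Conclusion.** The point holds for the first of the two readings. Under Section 7, viremia at the end of the fourth cycle is read at week 64 to 80, at the end of 8 to 12 weeks of resumed ART and before the final withdrawal. Its comparison with pre-HAART viremia would mainly show ART suppression. It also contradicts the item's own label, the three-determination definition, the primary goal and the set-point in Section 12.

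The timing rests on Section 7's order of events and needs no assumption about VL. The likely direction of the artefact rests on re-suppression, for which the protocol's support is its entry criterion and the cited 23 patients; it is not guaranteed in every patient. The 1.7 to 3.3 log10 range is illustrative, since it depends on an assumed pre-HAART VL.

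The end-of-study reading is not affected in the same way. It has a separate gap: patients who restarted ART under Section 7 would be on treatment then, and the protocol does not say how their values count.

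**What to change.** - **Time point.** In Sections 4 and 8a, take the first reading at the set-point reached after the final ART withdrawal, as Section 12 already does for the indication for ART. Keep the end-of-cycle VL only as a description of re-suppression.
- **All patients stay in.** Do not limit the comparison to off-ART values. That would drop patients who restarted, who are the failures of control, and would tilt the result towards success. In line with the intention-to-treat statement in Section 6e, keep every patient in the denominator. Count as not controlled those who restarted ART, were not withdrawn, or never reached a set-point. For restarters, the last off-ART VL before restart is an alternative where a level is needed. A patient who was never withdrawn has no post-withdrawal value. State the rule for both readings.
- **Cycle.** Reconcile the uses of the term in Sections 1, 7, 8 (calendar footnote) and 12, so that each analysis time point is fixed relative to the final ART stop. Which schedule applies is for the sponsor and investigators to settle.

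The cost is wording in Sections 4 and 8, a short handling rule in Section 12, and the reconciliation of terms. No extra samples are needed: the calendar already has VL every eight weeks after the stop up to week 136, then every four weeks.

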**9. Adverse events**

a) Reporting standards:

Description/definition: An adverse event is any undesired effect on a subject during their participation in a clinical trial and which is considered unrelated to the drug or drugs being studied. An adverse reaction is any detrimental and desired effect that occurs following the administration of a medication in the normal doses in a human being for prophylaxis, diagnosis or treatment of an illness.

Severity: Serious adverse events are those that lead to the death of a subject, the risk of death, persistent or significant disability, hospitalisation or the extension of hospitalisation, or congenital anomalies or neoplasia. (A situation involving “the risk of death” is one in which, in the doctor’s opinion, failing to have taken timely therapeutic intervention would have led to the death of the patient.)

Unexpected adverse events are those that are not described in the basic information of the product in terms of nature, severity or frequency.

Detection and registration method: adverse events will be monitored via careful clinical observation of the patient, laboratory analysis, spontaneous communication with the patient, and through open questioning.

Each event will be recorded in terms of its intensity, duration, the relation to the timing of the drug administration, the need for treatment and alternative possible causes.

b) Attribution criteria

With a view to analysing the possible cause and effect relationships, the following will be recorded: start and remission date, therapeutic measures adopted (none, interruption of treatment, treatment), evolution (full remission, after effects, persistence), persistence or otherwise following suspension of administration, or the reappearance with fresh administration of the drug. With a view to evaluating the attribution of the researcher, a five-point scale will be used.

c) Procedures for the immediate notification of serious or unexpected adverse events:

The main researcher will inform the coordinating centre of adverse events, and the latter will inform the health authorities. By informing the coordinating centre, the main investigator will not be relieved from the duty of informing the corresponding clinical research ethics commission (CEIC).

All adverse events that are detected throughout any period of the clinical trial will be communicated.

Any adverse event that leads to death, or that carries the risk of death, will be communicated to the trial supervisor within 24 hours.

Any adverse events that, whilst not carrying the risk of death, are serious or unexpected will be communicated via the notification form (see Annex V) within two weeks.

Any information relating to adverse events that are neither serious nor unexpected will be recorded in tables at the end of the clinical trial or at an interim analysis where applicable.

Information on serious adverse events, recorded in compliance with the *ex-ante* standards, will be submitted to the national medication agency (Agencia Española del Medicamento).

***

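### The Section 9a definition limits adverse events to those considered unrelated to the study drugs, contradicting the rest of Section 9 and leaving it unclear which events are counted and notified

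*Protocol*

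**What the plan says.** Protocol Section 9a gives two definitions. An adverse event is an undesired effect on a participant during the trial "which is considered unrelated to the drug or drugs being studied". The next sentence reads: "An adverse reaction is any detrimental and desired effect that occurs following the administration of a medication in the normal doses". Nothing in the protocol says that the first term includes the second.

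The safety variable in Section 8b is "Description of adverse events". Section 9c sets the general duty: "All adverse events that are detected throughout any period of the clinical trial will be communicated". It adds a fast rule: "Any adverse event that leads to death, or that carries the risk of death, will be communicated to the trial supervisor within 24 hours". It also gives a two-week rule for other serious or unexpected events, a rule for tabulating the remainder at the end of the trial or at an interim analysis, and a rule for submitting serious events to the national medicines agency. All of these are worded in terms of adverse events.

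Section 12, under descriptive analysis, uses the other term. It covers demographic variables and clinical events in the sample, "as well as adverse reactions in terms of absolute and relative frequency".

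**The concern.** In ordinary use an adverse event is any untoward occurrence, whatever its cause, and an adverse reaction is one attributed to the drug. Section 9a makes the broad term narrow. An investigator who follows it literally and judges a serious event to be caused by IL-2 could conclude that the 24-hour and two-week duties do not apply. Those are the events for which prompt notification matters most.

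It also matters for what the trial can conclude. Section 4 justifies the intervention partly on the ground that IL-2 at this level is free of side effects. Events attributed to IL-2 are the ones that test that premise. If it is unclear whether they belong to the safety variable, the tolerability result cannot be interpreted cleanly.

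**Working it through.** The protocol gives no figure to reproduce here. The check traces each use of the two terms and then follows an event through the rules.

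**Step 1. Which provisions use which term**

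| Provision | Term used |
| --- | --- |
| Safety variable, Section 8b | adverse events |
| General communication, Section 9c | adverse events |
| 24-hour rule, Section 9c | adverse event |
| Two-week rule, Section 9c | adverse events |
| End-of-trial tables, Section 9c | adverse events |
| Agency submission, Section 9c | serious adverse events |
| Descriptive analysis, Section 12 | adverse reactions (with clinical events) |

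One safety variable and five reporting rules depend on the first term. Apart from its own definition, the second term appears only in Section 12. It is in no notification rule.

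**Step 2. An event attributed to IL-2, read literally**

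- It is not an adverse event, because it is not considered unrelated. It therefore misses Section 8b and all five rules.
- As written, it is hardly an adverse reaction either, because a harmful effect would have to be *desired*. The definition also refers to normal doses, while Section 4 describes the trial dose as very low, so it is not clear that the dose qualifies.
- If *desired* is read as *undesired* and the trial dose is accepted as normal, the event is an adverse reaction and reaches the Section 12 frequencies. It still triggers no notification rule.

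**Step 3. The same event under the rest of Section 9**

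- Unexpected adverse events are those not described in the product's basic information. That test has a purpose only if adverse events can be caused by the product.
- Each event is recorded for its relation to the timing of drug administration and for alternative possible causes, so the drug is treated as a candidate cause.
- Section 9b records whether the event persists after the drug is stopped and whether it reappears when the drug is given again, in order to analyse cause and effect.
- Attribution is graded on five points. A graded scale would have little use if every adverse event were already unrelated. The definition also does not say at which grade an event would cease to be one.

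**Step 4. Comparison**

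Steps 2 and 3 cannot both describe the intended scope. The definition excludes related events; the operating provisions around it assume they are included. Section 12 does not settle the matter, because it uses the other term and creates no duty to notify.

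**The case against.** The strongest reply is that no one would run the trial on the literal definition. Section 9's unexpectedness, timing, re-administration and attribution provisions all show that related events were meant to be captured. *Detrimental and desired* in the adjoining sentence is plainly a slip, possibly one of translation, and the unrelatedness clause may be another. Drug-related harm is also picked up elsewhere: Section 7b has IL-2 tolerance evaluated at each visit and provides a safety commission, Section 6e records reasons for withdrawal, and Section 12 gives frequencies of adverse reactions.

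Much of this stands, and it limits the point in three ways.

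- A reader might infer that IL-2-related events are in fact excluded from the safety outcome and from every reporting rule. The documents do not support that as a settled consequence: it requires one clause to override the rest of Section 9.
- A reader might infer that Section 12 summarises only adverse reactions, so that Sections 8b and 12 describe two disjoint sets. Section 12 also covers clinical events in the sample, and Section 9c provides end-of-trial tables of adverse events. The adverse-reaction definition is also worded by what follows administration, not by the investigator's attribution, so the two terms are not clearly disjoint even when read literally.
- One patient in eight is 12.5%, but that only restates the sample size. It says nothing about how likely an event is to be misrouted.

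What does not stand is the suggestion that the text can be left alone. The tolerance check concerns suspending IL-2, and the Section 12 frequencies concern reporting at analysis; neither carries a 24-hour or two-week duty. That the intent can be guessed is a reason to write it down correctly.

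**Conclusion.** The point holds as an internal contradiction. The Section 9a definition of an adverse event is wrong as written, the definition of an adverse reaction contradicts itself, and Sections 8b, 9 and 12 do not use one term consistently. It is therefore unclear which events are counted in the safety variable and which must be notified.

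Its size is structural: one safety variable and five reporting rules depend on the faulty term, and followed literally they leave IL-2-attributed events with no notification duty. The documents do not show that the sponsor intended this or that it would happen in practice. The efficacy analyses are not affected.

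The conclusion rests on the current text alone. It assumes that no annex redefines the terms; the notification form in Annex V is cited but not shown. The correction should be made, because it is cheap and concerns patient safety.

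**What to change.** - **Section 9a, adverse event:** define it as any undesired occurrence during participation, whether or not it is considered related to the study drugs.
- **Section 9a, adverse reaction:** change *desired* to *undesired*, and make clear that the term means an event attributed to a study drug and is a subset of adverse events.
- **Sections 8b, 9 and 12:** use adverse event as the single governing term. Tabulate all adverse events and, within them, those attributed to IL-2 on the existing five-point scale.

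The cost is two sentences in Section 9a and about one line each in Sections 8b and 12. No new data are needed, because attribution and timing are already to be recorded for each event.
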